**Cell products and interventions**

***Cell isolation***

Cells will be primarily cultured by an enzyme digestion procedure of the explantation from patient’s own PDL tissue from the third molar using an aseptic technique. The extracted teeth will be rinsed with α-minimum essential medium (α-MEM, Invitrogen, Carlsbad, CA) containing 100 units/mL penicillin and 100 mg/mL streptomycin (Invitrogen) for 3 min for a total of 5 times. Next, the PDL will be gently separated from the surface of the root and digested in a solution of 0.2% collagenase type I (sigma) for 15 min at 37°C. Single cell suspensions will be obtained by passing the sample through an 80-mesh strainer, deposition at 1000 r/min for 8 minutes, and then blown in α-MEM supplemented with 10% fetal bovine serum (FBS). After cell counting, the cultures will be inoculated in 25-cm2 culture flasks with 4 mL of α-MEM medium at a concentration of 5×105 per flask and incubated in 5% CO2/95% air at 37°C. The culture medium will be changed once every two days until the cells grow to 80% confluence (7-10 days), at which time the cells will be passaged.

***Passage of cells***

After washing with phosphate buffered saline (PBS, Grand Island, NY, USA) to remove the remaining culture medium in the culture flask, the cells will be digested with 0.25% trypsin for 2 min at 37°C. α-MEM supplemented with 10% fetal bovine serum will be added to stop the digestion until the cells become circular and the majority are floating (observation made under reverse microscope). Cells will then be deposited at 800-1000 r/min for 6 minutes. Following the re-suspension of cells into PBS, a unicellular suspension will be used to inoculate the culture flask at a concentration of 5×105/mL. The cell type, passage, cell density, date and operators will be noted. The amount of cells at passage 4 will be 1×107 (passage time: approximately 20 days). The obtained cells will be identified by adipogenic and osteogenic differentiation.

To analyze the surface antigens, PDLSCs will be washed in PBS and then incubated with 2 μg/mL of the following mouse anti-human monoclonal antibodies: CD29, CD44, CD73, CD90, CD105, CD34, CD45, STRO-1 and CD146 for 30 min at 4 °C. To induce osteoblastic differentiation, 105 PDLSCs will be seeded in 6-well plates and cultured. When the cells reach subconfluence, the culture medium will be changed to DMEM containing ascorbic acid (L-ascorbic acid 2-phosphate) (50 μg/mL) (Sigma–Aldrich), dexamethasone (10−8 M) (Sigma–Aldrich) and β-glycerophosphate (10 mM) (Sigma–Aldrich). The culture medium will be changed every 3 days for either 14 or 28 days. For Alizarin Red staining, the cells will be fixed with 70% ethanol for 15 min at room temperature and stained using a 1% Alizarin Red solution for 5 min at room temperature. After staining, the culture plate will be washed with tap water and air-dried.

To induce adipocyte differentiation, 105 PDLSCs will be seeded in 6-well plates and cultured in growth medium. Adipocyte differentiation will be induced using adipocyte differentiation medium containing 1 μmol/L dexamethasone, 0.5 mmol/L IBMX, 10 μg/mL insulin, and 100 mmol/L Indomethacin until day 14. Next, the cells will be fixed using 70% ethanol for 15 min and washed twice with PBS. Oil Red O solution (Sigma) will then be added for 15 min, followed by rinsing of the plate with PBS.

***Cell sheets***

To create the cell sheet, the PDLSCs will be digested by trypsin to obtain single cell suspensions and then inoculated on 6-well plates at 1×105 per well with L-ascorbic acid (vitamin C; VC, 30 μg/mL, Sigma) until confluent (approximately day 10). Next, we will observe changes in cell morphology and sheet-forming capacity. After a 10-day culture, white membranous substances will appear on the bottom of the wells. Before clinical application, the culture medium will be discarded, and the cell sheets will be rinsed twice with phosphate-buffered saline (PBS; Gibco). Next, the 0.2-µm CBB particulates will be distributed onto the surface of the cell sheets at a concentration of 0.25 g per well. The PDLSC cell sheets will then be rolled up to pack the Bio-oss® particulates for clinical treatment.

***Interventions***

The surgical treatment will be performed in the region chosen for investigation. The Bio-oss® only (Control group) or Bio-oss®/cell sheets (Cell group) will be administered to the bone defect region. Each subject will receive a standard initial preparation prior to the surgical treatment, including oral hygiene instruction, full-mouth scaling, and root planning, to minimize the bacterial insult and reduce the variability between lesions at baseline.

**Safety assessment**

***Observation of subjective symptoms and objective findings***

Medical findings for both the oral cavity and whole body will be confirmed by interview and visual inspection.

***Clinical inspections***

The inspection items that will be measured and evaluated are shown below. In cases where we discover unusual changes in any of the clinical inspection values within 4 weeks after the administration of cells, a follow-up survey will be conducted.

- Hematological test (2 mL of blood)

Red blood cell count, white blood cell count, hemoglobin, hematocrit, platelet count, differential counts of leukocytes (neutrophils, eosinophils, basophils, lymphocytes, and monocytes)

- Biochemical blood test (2 mL of serum)

Total protein, albumin, blood urea nitrogen, creatinine, uric acid, total cholesterol, total bilirubin, aspartate aminotransferase, alanine aminotransferase, alkaline phosphatase, lactic dehydrogenase, C-reactive protein (CRP), creatine kinase (CK), Na, K, and Cl

- Urinalysis

Qualitative (10 mL of urine): protein, sugar, urobilinogen

Quantitative (3.5 mL of urine): urinary albumin (in creatinine equivalents), N-acetyl-beta-D-glucosamidase (NAG), beta2-microglobulin

- Blood glucose control index test (2 mL of blood): Conducted only before registration

Hemoglobin A1C

Pregnancy test (1 mL of urine): Conducted only before registration

Chorionic gonadotropin

***Measurement of antibody levels in serum***

The Department of Clinical Laboratory, Fourth Military Medical University School of Stomatology, will measure the levels of IgA, IgG, IgM, C3 and C4 in serum using ELISAs.

**Adverse events**

***Definition***

An adverse event is any unfavorable and unintended sign (including an abnormal laboratory finding), symptom, or disease that is temporally associated with the use of the investigational cells whether or not it is considered to be related to the investigational cells. We will examine the extent of any adverse events.

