**Methods/Design**

**Overview**

***Purpose***

The purpose of this clinical trial is to confirm the safety of autologous stem cells in clinical periodontal regenerative surgery and clarify the efficiency of autologous periodontal ligament (PDL) stem cells to form cell sheets that can be used to regenerate periodontal tissue in periodontitis patients with deep intraosseous defects (>5 mm). This study is a single-center, randomized, controlled study (Figure 1) that was approved by the ethical committees of School of Stomatology, Fourth Military Medical University (2011-02) and registered in the ClinicalTrials.gov database (reference no. NCT01357785). The study will be conducted according to the Declaration of Helsinki, and we will obtain consent from all enrolled subjects with regards to participation in this trial and contribution of trial data for non-commercial purposes. The protocol of this trial was externally reviewed and approved by an anonymous independent ethical review committee to ensure no serious ethical concerns. This study is a randomized clinical trial that includes a test and control group for comparison and involves only one dental facility (Translational Research Team, School of Stomatology, Fourth Military Medical University). The clinical trial will be conducted according to the schedule shown in Figure 1.

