***Main outcome measures***

In this study, we will examine the extent of adverse events related to the use of PDL cells. In addition to the safety assessment, the main outcome measure in the study protocol is the magnitude of change in the alveolar bone height (primary outcome for efficacy).

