**Study Design**

Each patient will be examined by at least five independent principal investigators. Investigator 1 will perform a basic oral examination using a clinical inspecting apparatus and X-ray, check all of the inclusion and exclusion criteria, and ensure that the informed consents are signed by the patients at the Registration Center. Next, Investigator 2 will perform the pre-surgical treatments, re-check the inclusion and exclusion criteria, and extract the tooth/teeth that will be subjected to cell isolation by Investigator 4. Investigator 2 will select no more than 2 teeth (from different regions) to be investigated in each patient. Following the collection of baseline data from the selected tooth/teeth by Investigator 3, Investigator 4 will culture the cells, make the cell products, and create an allocation table consisting of 2 cases per block that will be allocated to the Control group (Bio-oss® only) and Cell group (Bio-oss® and cell sheets). According to this allocation table, a label indicating the corresponding group will be attached to each tooth; thus, each tooth will be randomly assigned to one of the two treatment groups. The maximum number of teeth from one patient will be 2. Hence, if one tooth is allocated to the Control group, the other will be automatically assigned to the Cell group. However, if a patient only has one tooth chosen for investigation, it has a fair chance of being allocated to either group. Once a tooth is assigned to a group, it will be kept in a secure locked drawer inaccessible to all other study personnel. All of the patients will receive oral hygiene instructions, a tooth cleaning and basic dental therapies if needed, such as cavity filling and occlusal adjustment. The periodontal surgery will be performed 4-5 weeks after these pre-surgical treatments. When the oral condition and cell products are both ready for surgery, Investigator 4 will be asked to give the assigned implants (Bio-oss® only or a combination of Bio-oss® and cell sheets) to the physician (Investigator 5), who will then perform the surgery. This procedure ensures that the randomization is not influenced by the physicians taking part in this study. Investigator 4 will record the patients’ details and number the envelope assigned to each tooth. Investigator 3 will perform the follow-up study (data collection, safety assessment, etc.) of the patient, and the blind will not be broken until this clinical trial is completed.

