**Patients and enrolment**

Patients with periodontitis visiting our dental institution will be requested to participate. This study will be conducted in compliance with Good Clinical Practice guidelines. Prospective patients who provide written informed consent will undergo clinical inspection and an oral cavity diagnosis. We will then select approximately 30 patients (approximately 40 testing teeth) who satisfy the selection and exclusion criteria described below (most of these criteria were chosen from previous similar periodontal clinical trials [34,35]).

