***Evaluation of adverse events***

The investigators will record any adverse event with the exact name, onset date, severity, provided treatment and date of disappearance.

Each adverse event will be graded for severity using the following scale and criteria as outlined by the Ministry of Health and Welfare of the Chinese Government.

- **Mild**: The subject can continue the subsequent schedule without any treatment.
- **Moderate**: The subject can continue the subsequent schedule with treatment.
- **Severe**: The subject cannot continue the subsequent schedule.

The investigators will determine the relationship of the adverse event and the investigational cells.

The investigators will determine whether or not the adverse event is classified as a serious adverse event. A serious adverse event is defined as any experience suggesting a significant hazard, contraindication, side effect, or precaution. A serious adverse event includes any adverse experience resulting in any of the following outcomes:

- Death
- A life-threatening adverse experience
- Impatient hospitalization or prolongation of existing hospitalization
- A disability/incapacity that may interfere with the subject's daily life
- An adverse experience leading to a disability/incapacity
- A serious adverse experience at the same level as the above conditions
- A congenital anomaly/birth

**Efficacy assessment** [34,35]

The main outcome measure in the study protocol is change in the alveolar bone height at 3, 6, and 12 months post-operation. We set the rate of increase in alveolar bone height as the most statistically important outcome (primary outcome). The clinical attachment level (CAL), probing depth (PD), and gingival recession (GR) are generally used to assess pathology in periodontal disease. These parameters do not directly assess the efficacy of cells in periodontal tissue regeneration and were selected in the present study as secondary outcome measures to ascertain whether cells would cause abnormal periodontal healing following periodontal surgery. These measurements will be recorded at baseline and 12-months post-surgery.

***Standardized radiography and dental CT for regions of investigation*** [34,35]

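### The adverse event definition and the 4-week laboratory follow-up both run from use of the cells, so patients treated only with Control fall outside them and the blinded safety assessor cannot apply them

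*Protocol*

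**What the plan says.** The protocol's Purpose section puts safety first: "The purpose of this clinical trial is to confirm the safety of autologous stem cells in clinical periodontal regenerative surgery". Four passages then describe safety in terms of the cells.

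- **Adverse events, Definition:** an event is one "that is temporally associated with the use of the investigational cells whether or not it is considered to be related to the investigational cells".
- **Main outcome measures:** "In this study, we will examine the extent of adverse events related to the use of PDL cells".
- **Safety assessment, Clinical inspections:** for unusual laboratory changes found "within 4 weeks after the administration of cells, a follow-up survey will be conducted".
- **Evaluation of adverse events:** "The investigators will determine the relationship of the adverse event and the investigational cells".

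None of the four mentions the surgery, the bone mineral or the control procedure as a reference point.

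Under Study Design the tooth is the unit of randomisation, with at most two per patient. For a patient with two: "Hence, if one tooth is allocated to the Control group, the other will be automatically assigned to the Cell group". A patient with one study tooth has an even chance of either group. The same section gives safety follow-up to Investigator 3 and keeps the blind until the trial ends. Study Products confirms that this investigator does not know the treatment. On size, Patients and enrolment says: "We will then select approximately 30 patients (approximately 40 testing teeth").

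**The concern.** The words about relatedness in the definition remove only the causality condition. The timing condition remains, and it refers to an exposure that some patients never have. A patient given Control only has no date of cell use, so nothing that happens to that patient meets the definition and the 4-week laboratory window never opens.

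Both groups have the same periodontal surgery, so ordinary post-surgical events can be expected in both. If the definition were followed as written, the patients best placed to show the background rate of such events would contribute none. An event that is never recorded cannot be recovered at analysis.

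The rule also conflicts with the blind. Deciding whether an event is associated in time with cells requires knowing whether cells were given, and the person assigned to safety follow-up is not meant to know.

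**Working it through.** The protocol gives no adverse event rate, safety power or exposure count, so there is no figure of its own to reproduce. The check is how many patients the wording leaves out, and what their data could show once included.

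**Inputs.** Patients P = 30 and teeth T = 40, both approximate (Patients and enrolment). At most two teeth per patient, two-tooth patients split across groups, one-tooth patients allocated with even chance (Study Design).

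**Patients by exposure**
- Two-tooth patients: T − P = 40 − 30 = 10. All receive cells in one tooth.
- One-tooth patients: 30 − 10 = 20. Expected split: 10 Cell, 10 Control.
- Exposed to cells: 10 + 10 = 20. Never exposed: 10.

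**Sensitivity.** The expected Control-only number is (2P − T)/2.
- P = 28, T = 42: (56 − 42)/2 = 7.
- P = 32, T = 38: (64 − 38)/2 = 13.
- With exactly 20 one-tooth patients and simple 1:1 allocation, the 95% binomial range is 6 to 14. The planned blocks of two could hold it closer to 10.

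**The wording applied to each kind of patient**

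| Patient | Expected number | Date of cell use | Adverse event possible as defined | 4-week laboratory window |
|---|---|---|---|---|
| Two teeth | 10 | yes | yes | yes |
| One tooth, Cell | 10 | yes | yes | yes |
| One tooth, Control | 10 | none | no | none |

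The blinded assessor cannot tell the second row from the third. Only someone holding the allocation, or someone working after unblinding, could apply the definition as written.

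**Precision once all patients are covered.** With 0 events in n patients, the two-sided 95% upper limit is 1 − 0.025^(1/n).
- n = 10, Control only: 1 − 0.025^(1/10) = 0.308, or 31%.
- n = 20, any cells: 1 − 0.025^(1/20) = 0.168, or 17%.
- Two-sided exact Fisher power at 0.05 for 20 versus 10 patients, with assumed rates: 10% for 30% versus 10%, and 54% for 50% versus 10%.

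**Why the summary unit matters.** The roughly 20 Control teeth come from 20 patients, of whom 10 also received cells. If patient-level events were tabulated by tooth group, the apparent Control rate would be (10·p0 + 10·p1)/20, where p1 and p0 are the rates with and without cells. The apparent difference would be p1 − (p0 + p1)/2 = (p1 − p0)/2. With assumed rates of 30% and 10%, Control would show 20%, and the difference would be 10 points instead of 20. The protocol does not say that it will tabulate this way.

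**The case against.** The strongest reply is that this is loose wording and that practice would be sounder. Investigator 3 follows every patient under blind, so cannot discard events in Control patients and would probably record them all. The examinations, blood and urine tests and immunoglobulin measurements are not restricted to the Cell group. The laboratory sentence says when a follow-up survey is triggered; it does not say that Control results go unmeasured. Local events can be attributed to a tooth. The Efficacy assessment section also selects attachment level, probing depth and recession partly to detect abnormal healing, and these are measured on study teeth in both groups.

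Much of this stands. It defeats two stronger readings that a reader might infer. One is that the trial has no valid control rate for safety: the design contains about 10 patients without cells, and tooth-level comparisons exist in both groups. The other is that surgical events would in fact appear on the cell side only: that needs someone to filter events by allocation, which the blind is meant to prevent.

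The halved difference is also conditional. No tabulation of systemic events by tooth group is stated, and how patient-level events are summarised may properly sit in a statistical analysis plan that is not shown.

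What does not fall is the definition itself. It is protocol text governing what is collected. A rule that works only because the assessor cannot follow it should not be left in place.

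**Conclusion.** The concern holds as a defect of definition. Under the literal text, about 10 of about 30 patients can have no adverse event and no laboratory follow-up window, and the blinded assessor cannot apply either rule. The count assumes that the approximate 30 patients and 40 teeth are met and that one-tooth patients split evenly; modest departures give 7 to 13.

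The finding does not show that control safety data would be absent in practice, nor that a planned analysis is biased. Correcting the wording will not make the safety comparison precise either: the trial is small, and the 31% and 17% limits above apply after the correction. The reason to act is that safety is the first-named aim and the text describing what counts as an event conflicts with both the randomisation and the blind.

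**What to change.** 1. **Adverse events, Definition.** Replace the reference to use of the cells with: any untoward sign, symptom, disease or abnormal laboratory finding from study surgery to month 12, in every treated patient, whichever group, whether or not considered related to the treatment.
2. **Clinical inspections.** Replace administration of cells with study surgery as the start of the 4-week window.
3. **Before surgery.** List any events between tooth extraction and surgery separately. They precede surgery in both groups, and including them in the main count would dilute a comparison of what follows it.
4. **Summaries, here or in the analysis plan.** Present patient-level events, laboratory values and immunoglobulins as patients with any Cell tooth versus patients with a Control tooth only. Present local events by tooth.

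The cost is two wording changes, a separate listing and one extra table, with no added visits or tests. The downside is that more events will be recorded in Control-only patients, and their rate, from about 10 patients, should be reported with its interval and not treated as a precise background figure.

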***Evaluation of adverse events***

The investigators will record any adverse event with the exact name, onset date, severity, provided treatment and date of disappearance.

Each adverse event will be graded for severity using the following scale and criteria as outlined by the Ministry of Health and Welfare of the Chinese Government.

- **Mild**: The subject can continue the subsequent schedule without any treatment.
- **Moderate**: The subject can continue the subsequent schedule with treatment.
- **Severe**: The subject cannot continue the subsequent schedule.

The investigators will determine the relationship of the adverse event and the investigational cells.

The investigators will determine whether or not the adverse event is classified as a serious adverse event. A serious adverse event is defined as any experience suggesting a significant hazard, contraindication, side effect, or precaution. A serious adverse event includes any adverse experience resulting in any of the following outcomes:

- Death
- A life-threatening adverse experience
- Impatient hospitalization or prolongation of existing hospitalization
- A disability/incapacity that may interfere with the subject's daily life
- An adverse experience leading to a disability/incapacity
- A serious adverse experience at the same level as the above conditions
- A congenital anomaly/birth

**Efficacy assessment** [34,35]

The main outcome measure in the study protocol is change in the alveolar bone height at 3, 6, and 12 months post-operation. We set the rate of increase in alveolar bone height as the most statistically important outcome (primary outcome). The clinical attachment level (CAL), probing depth (PD), and gingival recession (GR) are generally used to assess pathology in periodontal disease. These parameters do not directly assess the efficacy of cells in periodontal tissue regeneration and were selected in the present study as secondary outcome measures to ascertain whether cells would cause abnormal periodontal healing following periodontal surgery. These measurements will be recorded at baseline and 12-months post-surgery.

***Standardized radiography and dental CT for regions of investigation*** [34,35]

Our geometrically standardized radiography employs dental film (Kodak InSight Super Poly-Soft; Eastman Kodak Company, New York, USA) and photograph indicators (Cone Indicator-II; Hanshin Technical Laboratory, Hyogo, Japan) that are customized with resin stents. Two doctors specializing in dental radiology from the Department of Oral Diagnosis at Fourth Military Medical University School of Stomatology will measure the changes in the alveolar bone height (%) using the methods described below (Figure 2). Each examiner blinded to the treatment conditions will independently measure this value, and the median of 2 measurements taken from the same image will be selected for analysis. In addition, a dental CT that reports data automatically will be used to assess bone regeneration in selected cases. These data will be used for information purposes only or as a reference for the design of subsequent trials (not included in the analysis of this trial).

[figure not shown]

**Figure 2**. Schematic illustration of the bone regeneration assessment using standardized radiography. Points C, A and B represent the cementoenamel junction, apex and bottom of the bone defect, respectively. The examiner measured the tooth axis heights between Points C and A and between Points C and B (bone-defect depth, BDD) on the X-ray for each patient. To adjust for slight errors due to imaging, the measurements from 5 examiners were multiplied by the A-C ratio of the before to after administration to correct for C-B after administration. Based on C-B data before surgery and during follow-up (3, 6 and 12 months), increse of BDD was calculated to serve as an indicator of increase in alveolar bone height post-operation [37,38].

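### Adverse-event severity is graded by ability to continue the schedule rather than by intensity, so after a single graft surgery it separates moderate from severe harm poorly

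*Protocol*

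**What the plan says.** The Protocol, under Evaluation of adverse events, defines three severity grades. The top grade, severe, is reserved for the case where "The subject cannot continue the subsequent schedule". The middle grade, moderate, is worded as follows: "The subject can continue the subsequent schedule with treatment". The lowest grade, mild, differs from the middle one only in that no treatment is needed.

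It presents them as an official scale, with events graded "using the following scale and criteria as outlined by the Ministry of Health and Welfare of the Chinese Government". The adverse-event section does not say what the schedule in question contains.

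The same section has a second, separate classification: "The investigators will determine whether or not the adverse event is classified as a serious adverse event". Seven qualifying outcomes follow, among them death, a life-threatening event and hospitalisation. For every event the investigators also record its name, when it began and ended, how it was treated, and their judgement of its relation to the cells.

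On the intervention, the Interventions section says "The surgical treatment will be performed in the region chosen for investigation", with the assigned graft placed in the bone defect. On the role of safety, the Purpose paragraph puts it first, and Main outcome measures says "we will examine the extent of adverse events related to the use of PDL cells".

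**The concern.** A scale built on whether the subject can go on works best when treatment is repeated: an event that stops the next dose is in a meaningful sense worse than one that does not. Here there is no next dose to stop. Once the graft is in place, the subject mainly has assessments to attend, and many harmful events that are treated and resolve leave that possible. The grade then reflects whether follow-up could go on and whether treatment was given. It does not reflect how bad the event was.

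What is at stake is the safety description, which is a main aim of the trial. A minor symptom treated with a simple remedy and a graft-site infection that needs a hospital stay can carry the same grade. A table of events by severity could then be read as a statement about intensity that the scale does not support. With approximately 30 patients, one patient is about 3.3% of the sample (1/30), so the grading of a few events can change the look of the summary.

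**Working it through.** The protocol states no figure on this point, so the check is one of definitions.

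**Step 1. What the grade depends on.** The three definitions use two yes/no questions: can the subject continue, and was treatment needed?

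| Can continue? | Treatment? | Grade |
|---|---|---|
| Yes | No | Mild |
| Yes | Yes | Moderate |
| No | Either | Severe |

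Peak intensity, duration and effect on function appear nowhere.

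**Step 2. What is left to continue.** Single administration is not stated in so many words, but the text points to it:

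- Study Design describes one periodontal surgery at which the assigned implant is handed to the surgeon, followed by data collection and safety assessment.
- Clinical inspections counts its 4-week window from the administration of the cells, as one event.
- Exclusion criteria rule out patients with another operation planned near the test tooth within 36 weeks of surgery, which fits poorly with repeat grafting.
- Statistics speaks of teeth receiving at least one therapy, but that sentence defines the analysis set. It is not a dosing plan.

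After surgery the text describes radiographs at 3, 6 and 12 months, clinical measurements at 12 months, and safety follow-up. No later dose is described.

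**Step 3. The grades applied to the protocol's own serious-event list.**

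| Listed outcome | Must be Severe? |
|---|---|
| Death | Yes |
| Life-threatening event | No |
| Hospitalisation or longer stay | No |
| Disability affecting daily life | No |
| Event leading to disability | No |
| Event of comparable seriousness | No |
| Congenital anomaly | No |

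One of seven outcomes necessarily forces the top grade. The other 7 − 1 = 6 can be graded moderate if treated and the subject can still be followed; on the literal wording they could even be mild if untreated. For example, "Impatient hospitalization or prolongation of existing hospitalization" makes an event serious, yet a subject who is treated, discharged and able to go on meets the moderate definition.

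**Step 4. Events that are intense but not serious.** These meet no item on the list, so severity is the only graded item that could set them apart. From Step 1 it does not: if treated, they share a grade with any minor treated event. The other recorded items (name, dates, treatment, relation to the cells) give indirect hints only.

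**The case against.** The strongest reply is that the serious-event classification in the same section already catches the worst cases. Hospitalisation and life-threatening events are both named there. Severity and seriousness are different attributes, so a serious event graded moderate is not a contradiction in itself. This stands: serious harm would still be identified. It does not help with intense events that meet no serious criterion.

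Second, whether a subject can continue is an investigator's judgement, and an investigator might call a life-threatening reaction severe. That is possible, but nothing in the definitions asks for it, so two investigators could grade the same event differently and both be within the text.

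Third, the scale is attributed to a ministry and its use may have been required; the source cannot be checked here. That is a reason to keep it, but not a reason to use it alone.

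Fourth, Statistics plans no test on severity grades, and an analysis plan may say more about safety summaries. Both points are fair. But the grade is assigned when the event occurs, and an analysis plan cannot recover an intensity that was never recorded.

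A reader might go further and infer that the severe grade is practically out of reach, that a report of no severe events is built into the scale, or that any event resolved within the 3- or 6-month gap between radiographs cannot exceed moderate. The documents do not support these readings. Death, withdrawal because of an event and, arguably, loss of the test tooth all fit the severe definition, and no event rates are given. The 3-, 6- and 12-month times are those of the radiographs, not shown to be the full visit plan: the Overview refers to Figure 1 for the schedule, which was not available in the text reviewed, and Clinical inspections implies safety contact within 4 weeks of surgery.

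**Conclusion.** The point holds as a weakness in how severity is recorded. The scale separates moderate from severe harm poorly, because it asks about continuing the schedule and about treatment, never about intensity. Six of the seven listed serious outcomes can sit below the top grade, and intense non-serious events are not distinguished at all.

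This rests on the literal wording of the grades and on reading the graft as a single administration, which the text strongly suggests without saying so. The effect is confined to the severity profile. Serious harm is still flagged by its own classification, and the primary outcome, sample size and significance level are not affected. How often a grade would mislead cannot be estimated from the protocol. It is a cheap improvement worth making because safety is a main aim.

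**What to change.** Keep the ministry scale if it is required, and add one graded item to the adverse-event form. Suggested protocol text:

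> In addition to the ministry scale, the investigator will grade each adverse event for its worst intensity and its effect on function. This grade will not depend on whether the subject continues in the study. Safety conclusions will be based on this grade together with the list of serious adverse events.

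The anchors for the new grade should be written on the form, so that investigators apply them alike. The protocol should also say what the schedule in the ministry scale refers to, so that the existing grade can be interpreted.

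The cost is one form field and a short paragraph; no visit or staff time of note is added, and treatment of events is unchanged. The downside is that the reported severity profile may look less favourable than under the present scale alone.
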